**Fig. 1 Fig1:**
[figure not shown]
Design of wait-list control randomized controlled trial of school salad bars

Each pair of Intervention and Control schools will be assessed concurrently, minimizing the threats maturation and history effects pose to internal validity [45]. Baseline and post-assessments within each pair will be conducted on days with the same menu cycle whenever possible, which controls for potential confounds, such as the varying palatability of meals and seasonal variations in food availability (the district’s schools have 5 week menu cycles). We will also control for month of assessment in all analyses. This is particularly important in the elementary school setting, where students are continually adjusting to the environment and school breaks can affect eating habits [46]. Inclusion of baseline assessments will allow us to control for any baseline differences between schools. Raters will be masked to avoid potential bias. Moreover, conducting independent double ratings of ~ 20% of meals will further minimize the influence of any potential bias. Finally, this study’s internal validity is enhanced by matching schools on key variables prior to randomization, so that they differ primarily on presence of a salad bar [45]. Matching procedures were carefully developed to evaluate how school-level factors of race/ethnicity and SES might moderate the impact of salad bars. Other variables that could potentially vary between schools and impact outcomes will be carefully monitored and considered in analyses (e.g., NSLP participation or school environment factors). Plate waste assessments will be conducted in wait list control schools during two consecutive years; however, students will not know the purpose of the assessments, and their prior experience with these (minimally obtrusive) methods is not likely to alter dietary behaviors during the following school year.

### Target population and sample

The school district included in this study serves > 189,000 elementary school students (K-6th grades); 48 of its 141 elementary schools are Title I, and 31% (> 58,500) of students receive free and reduced-price lunch (1-91% across schools). Students are 40% White, 25% Latinx, 19% Asian, 10% African American/Black, and 5% more than one race. These data highlight the great diversity of this district with respect to SES and race/ethnicity, making it an ideal setting in which to examine if the potential differential impact of salad bars based on these school-level factors. Potential schools have a mean enrollment of 692 students and mean NSLP participation rate of 53% (range 23–85% [national rate is 61%]) [43].

Lunches from all children who participate in the NSLP on rating days will be eligible. We conservatively estimate rating ~ 295 lunches (~ 80% of NSLP participants) per school on each assessment date, from K-6th grade students, with equal grade distributions. This rate is consistent with those achieved in our formative work [28]. We thus anticipate rating 7,080 lunches (3,540 per condition) at baseline and post-assessments across 12 pairs of matched schools, for a total of ~ 14,160 school lunch observations throughout the study duration. To inform understanding of barriers and facilitators to salad bars, cafeteria personnel from target schools will complete weekly logs and post-surveys assessing their perspectives related to salad bars; there are 4–7 staff per school, from diverse backgrounds. With an 80% response rate, consistent with rates we achieved previously, [47] we anticipate that ~ 70 cafeteria staff will participate.

The district’s Food and Nutrition Services staff conduct a standardized training for all students and staff prior to their salad bar launch. Student training includes informing students that salad bars will replace all other FVs on the lunch line, describing what foods will be offered, and instruction related to proper salad bar use (e.g., sanitation, food safety and handling, and portion and food group guidelines). Trainers also provide education related to the importance of consuming FVs, developmentally tailored based on grade-level. Staff training includes strategies to ensure USDA adherence related to portion sizes and food groups, monitoring and implementation protocols, menus, food preparation, storage and handling, and cashier training. Cashiers are trained to ensure meals adhere to NSLP guidelines (e.g., ≥½c FV), with strategies taught to facilitate visual estimation of this portion.

All students encounter the salad bars as the first option in the lunch line. This placement is consistent across schools and intentional, as placing healthier foods first in line increases their selection [48]. Further, Adams et al. reported that FV selection and consumption was more than 4 times greater in schools with salad bars located within the serving line, prior to the point of purchase, compared with those located outside the line, after the point of purchase [41]. This district’s salad bars include FVs (7 options [all fresh] that rotate based on seasonal availability) and 2 proteins, with the option to also select a whole grain and milk from the second part of the line. Salad greens and dressing (1oz serving) are always offered. Salad bar menus are consistent across schools. FV portions must adhere to USDA serving size guidelines for the NSLP. To facilitate meeting these requirements, lunch trays have an identified “square” to fill with any combination of FVs desired. Signage also facilitates adherence with NSLP guidelines (e.g., use of colored stars for each food group). In addition, cafeteria staff monitor salad bars on the line to ensure students serve adequate FV portions. If students’ trays do not meet USDA requirements, staff guide them back to the salad bar to select additional fruit or vegetable options before ringing in the meal. Once installed, salad bars replace all other FVs on the serving line, thus students must select FVs from the salad bar. Moreover, students can choose to select their entire meal from the salad bar and bypass the hot meal completely. Thus, in the current investigation, we will be able to investigate how FV presentation (self-serve vs. fixed portions) and location impact dietary intake, within the NSLP.

### Cafeteria assessor and digital imagery (DI) rater training

Masked cafeteria assessors and DI raters will be trained following detailed protocols used in previous research, which yielded excellent inter-rater reliabilities (IRRs), maintained throughout the trial [28, 40].

Cafeteria assessors will participate in a standardized training that includes details of cafeteria procedures, in addition to extensive practice taking photographs from a standard angle (45°) and distance using mock trays. Feedback will be provided until methods are consistently applied.

Independent raters (masked to timepoint and study hypotheses) will be trained according to protocols to rate item selection and consumption from the photographs. Raters will view multiple images of plated and post-consumption trays from previous salad bar investigations. They will indicate the % of each item consumed in 20% increments [49–51]. Because of the variable reference portions from salad bars, raters will be carefully trained to assess portion sizes and volume visually (to the nearest ¼c) for different servings of FVs (that had been previously measured) using photographs and standard portions as a guide, consistent with our previously validated methods [52]. Raters must achieve IRRs (assessed via ICCs) of ≥ 0.80 for all items evaluated, as well as ICCs ≥ 0.80 when compared with “gold standard” ratings to indicate readiness to participate in the study.

## Measures

### Cafeteria environment

Prior to baseline, we will obtain details about each school via systematic observations and reports from the district’s Food and Nutrition Services to include: (1) number of points of sale, (2) lunch period length (if different from 30 min district standard), (3) lunch time per grade, (4) presence of a school garden, (5) other relevant programs (e.g., Farm to School programming); (6) free and reduced-price lunch and NSLP participation rates; (7) other food environment aspects that might vary between schools. These factors will be considered in analyses as potential explanations of any differential impact of salad bars across schools.

### Demographics

School, sex, and grade will be obtained from labels affixed to trays (See Procedures). On rating days at each school, study staff will obtain updated enrollment data, number of students absent per grade, number of lunches brought from home per grade based on the average of two rater counts, and number of student and parent opt-outs (to determine study participation rate).

### FV selection

Raters will note which items were available and selected, including number and types of FVs (coded with a location). Vegetables will be categorized as dark green, red/orange, legumes, starchy, and other, consistent with USDA/NSLP [44]. Fruit is defined as whole fruit (not juice). *Variety* will be scored as the number of different types of FVs and as the number of different categories of vegetables the student selected. *Location* (salad bar, lunch line, or point of sale) and serving type (self-serve, pre-portioned) of each FV will be obtained from photographs of the lunch line.

### Plate waste

Raters will estimate the % of each item consumed in 20% increments. Visual stimuli (pie charts) on a validated tick sheet assist raters in making judgments [53]. Ounces remaining (to the nearest 0.5oz, assessed in the photographs of measuring cups) will be used to determine % consumed for beverages, consistent with methods applied previously [49]. Plate waste (%) and % consumed will be determined for (1) FVs, (2) non-FVs, and (3) beverages. The average % consumed for all salad bar components will be calculated and applied to dressing (if used) to calculate consumption. These methods are consistent with those used in our prior salad bar investigation, yielding excellent IRRs [40].

### Nutritional information

Recipe data from standard portions (average of 3 measured portions) and all items from the salad bar will be entered into the Nutrition Data System for Research (NDSR) [54, 55] for analysis. The amount missing will be assumed to have been consumed, [16, 49, 56] and subtracted from the plated portion. FV, non-FV, beverage, and total energy (kcal) available and consumed will be calculated. The Healthy Eating Index (HEI) 2015 [57] will assess dietary quality of the lunch; scores for each component will be calculated from NDSR data, [57] and a total HEI score (possible range = 0-100) for the meal will be created. The HEI 2015 was developed by the USDA and the National Cancer Institute to evaluate dietary quality compared with current USDA guidelines.

### Sales data

Monthly NSLP participation rates, FV sales/reimbursements, and salad bar sales/reimbursements (including whether the salad bar was part of a NSLP meal or a la carte [Intervention schools]), and number of days lunch was served per month will be obtained from the district for all selected schools.

### Cafeteria staff survey

At post-testing, cafeteria staff will be asked to complete a survey based on our formative work [47] and in previous investigations [58–60] to assess perceptions of the school food environment, perceived barriers and facilitators to salad bars, satisfaction with staff and student training, impact of salad bars on daily work, and suggestions for improvement. Responses will identify barriers and facilitators to salad bar programs to inform their sustainability and will be considered as potential factors explaining any differential findings between schools. Surveys will be anonymous and available in the preferred languages of each cafeteria personnel. To increase participation, respondents will have the option to enter a raffle for a $25 gift card. These methods yielded high response rates in our prior work [47].

### Process logs

Cafeteria managers at the target schools will complete process logs for 4 weeks after salad bars are installed, assessing implementation practices (e.g., location of salad bar, monitoring, menu) and any aberrations from protocols. Managers will receive a $25 gift card for completion of logs. Food and Nutrition Services staff will provide any modifications to salad bar training or methods. We will also monitor any changes to NSLP or school/district policies that might impact the current investigation for consideration in analyses.

## Procedures

### Consent

Passive consent will be used; students can refuse to have their tray imaged without penalty. Parents/caregivers will be informed of the study via notification letters sent home by the schools, with a form to return if they wish to opt their child out of assessments. On rating days, teachers will read a short script to students prior to lunch to inform them about ratings occurring in the cafeteria, noting that participation is voluntary.

### Cafeteria procedures

Lunchroom observations will be conducted in randomly selected, matched pairs of schools by trained assessors (typically graduate and undergraduate students in psychology, nutrition, or public health). Each matched school pair will be rated concurrently, before (baseline) and 4–6 weeks after salad bars are installed (post), for menu consistency. Lunch selection and consumption will be assessed using the validated DI methods described, [49, 51, 61] and implemented successfully in our prior work [28, 52] . As students enter the lunch line (in grade groups), staff will obtain their assent. If students agree, they will affix a label on their tray (with grade recorded). Labels are color-coded and numbered to track sex and facilitate subsequent rating by matching pre- and post-consumption images. As students exit the lunch line, research staff will place their tray on a reference table to standardize the distance and take a photograph. All photographs will be taken digitally with iPads at a standard distance and ~ 45° angle from the meal [16, 62, 63].  The number of students who bring a lunch from home per grade will be independently counted by two raters and an averaged used. If food from home (typically drinks and snacks) is added to the school meal, it will be included in the photograph and subsequently rated if it is visible at both pre- and post-consumption. Trash cans will be moved during observations, except for those staffed by raters. Upon completion of each lunch period, students will be instructed to leave their trays on the lunch table. Staff then prepare each tray for rating. They reposition items to ensure the label and all items are visible. Beverage waste is poured into a clear measuring cup to facilitate rating  [63]. Containers for unopened beverages are left unopened and positioned upright; containers for empty beverages are placed on their side. If opened, pre-packaged items (e.g., chips) are removed from packages. We developed this method in our formative work to facilitate estimation of intake in the lab and overcome lower reliabilities found for packaged food in a prior plate waste study [64]. Staff will then take another image documenting what was left unconsumed. Trays are then discarded and tables cleaned for the next lunch period. See Fig. 2. On rating days, staff will make detailed process observations and two raters will independently count the number of lunches brought from home (by grade).

**Fig. 2 Fig2:**
[figure not shown]
Pre-consumption (**a**) and post-consumption (**b**) image of a school meal using digital imagery methods

Images will be subsequently uploaded onto computers in the lab to prepare for rating. After post-ratings, staff will distribute FV-themed pencils or other small incentive to all children (regardless of participation), as tokens of appreciation. We have found that ~ 10–15 staff per school (to administer labels, take photographs, prepare trays for imaging, and clean-up) optimizes rating efficiency and minimizes disruptions to cafeteria flow (an extremely high priority for school staff). Benefits of DI are the rapid acquisition of data in the cafeteria environment (< 5 s per tray), [63, 64] low staff and school burden, and ability to conduct objective ratings in an unhurried laboratory setting. Moreover, both rater agreement and validity for estimating portion sizes and waste using DI methods, including those from salad bars, are very high [52, 62, 63].

On each rating day, study dietitians will verify all foods against school menus. Photographs of the lunch line will be taken to document placement of FVs, including salad bars. Photographs and direct measurements (using a calibrated food scale) of 3 portions of each item will be taken and an average used as the reference for a standard portion. Serving sizes, product information and recipes of all items offered will be obtained from the district’s dietitian after each rating period, for entry into NDSR and subsequent analyses.

### Salad bar reference portions

Given variable portions of self-serve salad bar items, we will use methods described previously [52] to create reference portions of all salad bar menu items. Food will be prepared in the lab, using methods consistent with those used in the schools (e.g., diced, sliced, or whole). Two dietitians will independently serve 3 portions of each item (½c, ¼c, ¾c, and 1c) onto cafeteria trays. Portions will be weighed in triplicate (after taring to remove the weight of the tray), and an average used as the reference weight. Staff will take photographs of these portions for use by DI raters when estimating starting portions from salad bars.

### DI rating procedures

In the lab, trained, masked, independent raters will simultaneously view the images of the food selection and waste for each tray on a computer screen [49–51]. Raters will record which items were selected and then estimate the % of each item (FVs, non-FVs, beverages) left on the plate. Given variable reference portions for salad bar items, raters will estimate the plated volume of FVs selected to the nearest ¼c, consistent with prior research [13, 65]. Reference images of each salad bar item in standard portions will be available to assist raters in making judgements. Salad dressing usage (Y/N and type [ranch or Italian]) will be recorded and standard serving sizes (1oz) applied. Schools use a 24oz bottle of each dressing and monitor usage in daily production records. Per the school district, 25–35% of students use salad dressing (based on the assumption that 1oz is used per child), which is consistent with objective assessments in prior research [29]. Further, the district’s salad bar coordinators reported that over-portioning has not been an issue, likely due in part to close monitoring by staff. However, given potential for caloric intake to vary based on salad dressing portion applied, we will monitor usage and adjust rating methods accordingly. Foods brought from home will be noted and will only be rated if the student also purchased a school lunch (i.e., went through the lunch line and had a pre-consumption photograph taken), and if the non-school food is present in both the pre- and post-consumption photograph. At least 20% of images will be double rated and IRRs calculated for each item. If IRRs fall below 0.80, raters will be retrained and images re-rated. We have demonstrated our ability to achieve and maintain extremely high IRRs using these methods [28]. We also validated use of DI against measured weights to estimate volume and waste from salad bars and demonstrated excellent IRRs (ICCs = 0.91) and accuracy for both starting portions (ICC = 0.74) and waste (ICC = 0.98) across vegetables [52].

## Statistical analyses

### Power analysis

Power and effect size of the multilevel models that will be used to analyze the variety of outcomes in our cluster RCT are a function of a number of parameters: (1) the number of clusters (J = 16 independent schools [8 Intervention and 8 Control]), (2) the cluster size (*n* = 295 lunches per school), and (3) the ICC (estimated as 0.01, 0.05, and a much more conservative 0.10), which takes into account the correlated nature of our data and is the ratio of variability between clusters to the total variability [66]. Optimal Design Plus Empirical Evidence v3.01 software [67] was used to calculate the minimum detectable effect size given the parameters above, α = 0.05, and a desired power of 80%. For ICCs of 0.01, 0.05, and 0.10, we have 80% power to detect small to medium effect sizes of 0.17, 0.35, and 0.48, respectively. Thus, our proposed sample of 14,160 observations will be more than adequate to evaluate the study aims.

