As illustrated in Fig. 1 and 16 different schools will be included (A1➔D4), 4 from each sociodemographic category. In Year 1, 8 schools will be randomly selected: 4 with salad bars (A1➔D1; Intervention), matched with 4 serving pre-portioned FVs only (A2➔D2; Control). In Year 2, these 4 control schools will receive salad bars and become Intervention schools, and will be matched with 4 new, randomly selected Control schools (A3➔D3). These procedures will be repeated in Year 3, with A3➔D3 becoming Intervention schools, matched with new randomly selected Control schools (A4➔D4). There will ultimately be 12 pairs of matched schools (12 Intervention [shaded green in Fig. 1] and 12 Control [shaded yellow]).

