### Analyses

Prior to analyses, distributions of all measures will be examined. Contingency tables and frequency distributions will be evaluated (for categorical and continuous variables, respectively), and transformations considered. Outliers will be checked for errors before being used in analyses. Sex differences will be assessed for all outcomes; if significant differences are found, analyses outlined below will be stratified by sex. All tests will be 2-sided at α = 0.05 level, corrected for multiple comparisons, and conducted in SAS v9.3.

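### The stated 80% power belongs to a single-time-point comparison of 8 versus 8 independent schools at uncorrected 0.05, which is neither the design nor the test described

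*Protocol article*

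**What the plan says.** All references are to the protocol article.

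- **Power analysis.** The inputs are "the number of clusters (J = 16 independent schools [8 Intervention and 8 Control"]), a cluster size of "295 lunches per school", ICCs "estimated as 0.01, 0.05, and a much more conservative 0.10", alpha 0.05 and 80% power. The stated MDES are 0.17, 0.35 and 0.48. The section concludes that "our proposed sample of 14,160 observations will be more than adequate to evaluate the study aims".
- **Target population and sample.** The 295 is a count for one visit: "We conservatively estimate rating ~ 295 lunches (~ 80% of NSLP participants) per school on each assessment date".
- **Design.** "There will ultimately be 12 pairs of matched schools", built over three years from 16 schools. Year 1 controls become Year 2 Intervention schools, and Year 2 controls become Year 3 Intervention schools. The primary dependent variable is the change in FV intake, assessed at baseline and post.
- **Analyses.** "All tests will be 2-sided at α = 0.05 level, corrected for multiple comparisons, and conducted in SAS v9.3". The models are multilevel, with students nested in schools. Plate-waste ratings for the primary outcome are to be calculated for fruits, for vegetables, for each category and as an average.

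**The concern.** A power statement is useful only if it refers to the contrast that will be tested. Here four features of the calculation differ from the plan: the allocation of schools to arms, the use of baseline, the significance level, and the sample to which the conclusion is attached.

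The last is more than wording. With about 295 lunches per school, precision is governed mainly by the number of schools and the stability of their means, and hardly by the number of trays. The Discussion reasons from lunch counts again when it expresses optimism about power should data collection not resume after the COVID-19 pause. A reader cannot tell from the stated figures what effect on change the design can detect.

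**Working it through.** **1. Reproduce the stated figures.**

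Inputs (Power analysis): J = 16 split 8/8, n = 295, ICC = 0.01, 0.05, 0.10, two-sided alpha 0.05, power 80%.

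For one measurement per school, in units of the lunch-level standard deviation: Var = (4/J)[ICC + (1 − ICC)/n]. With a noncentral t on J − 2 = 14 df, the MDES is 3.013 × √Var.

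| ICC | Var | MDES | Stated |
|---|---|---|---|
| 0.01 | 0.25 × (0.01 + 0.99/295) = 0.00334 | 0.174 | 0.17 |
| 0.05 | 0.25 × (0.05 + 0.95/295) = 0.01331 | 0.348 | 0.35 |
| 0.10 | 0.25 × (0.10 + 0.90/295) = 0.02576 | 0.484 | 0.48 |

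The alternatives tried do not give the stated set:

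- J = 24: 0.138/0.276/0.384
- n = 590: 0.163/0.342/0.480
- one-sided: 0.151/0.302/0.420
- normal approximation: 0.162/0.323/0.450

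The article does not call its calculation single-time-point. That follows from the cluster size, the absence of any baseline term, and this match.

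**2. Compare with the design.**

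| School set | Year 1 | Year 2 | Year 3 |
|---|---|---|---|
| A1–D1 | Intervention | – | – |
| A2–D2 | Control | Intervention | – |
| A3–D3 | – | Control | Intervention |
| A4–D4 | – | – | Control |

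Four schools are Intervention only, four are Control only, and eight serve in both arms. That makes 12 + 12 = 24 school-years, so an 8/8 split of independent schools never occurs.

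**3. Compare the sample counts.**

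The calculation uses 16 × 295 = 4,720 lunches. The concluding sentence refers to 24 × 295 × 2 = 14,160.

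**4. Approximate the contrast on change.**

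Assumptions not in the document: r is the correlation of a school's baseline and post means; trays are not linked between visits; matching brings no gain; the 12 pairs are independent.

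The variance of one school's change is 2[ICC(1 − r) + (1 − ICC)/n]. The difference within a pair doubles this, and averaging over 12 pairs gives Var = (4/12)[ICC(1 − r) + (1 − ICC)/n]. On 11 df the MDES is 3.078 × √Var. At ICC 0.05 and uncorrected two-sided 0.05:

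| r | Var | MDES |
|---|---|---|
| 0 | (0.05000 + 0.00322)/3 = 0.01774 | 0.41 |
| 0.3 | (0.03500 + 0.00322)/3 = 0.01274 | 0.35 |
| 0.5 | (0.02500 + 0.00322)/3 = 0.00941 | 0.30 |
| 0.8 | (0.01000 + 0.00322)/3 = 0.00441 | 0.20 |

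Over r = 0, 0.5, 0.8 the values are 0.205/0.162/0.130 at ICC 0.01 and 0.571/0.409/0.270 at ICC 0.10.

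**5. Effect of a multiplicity correction.**

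The article names neither method nor family. As an illustration only, Bonferroni over three tests (alpha 0.05/3) at ICC 0.05 gives 0.497, 0.362 and 0.248 for r = 0, 0.5 and 0.8.

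**The case against.** The arithmetic is correct for the model used, and 14,160 agrees with the sample described elsewhere in the article. The 8/8 model could also be defended as a cautious simplification: it counts 16 distinct schools rather than 24 school-years and takes no credit for baseline or matching. A condensed article may leave the multiplicity family and the baseline-to-post correlation to a fuller document.

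Much of this stands. There is no computational slip, and the absence of a named correction method is not the point here. However, the article does not present 8/8 as a simplification; it states it as the allocation, against its own Design section. Nor is caution assured: at r = 0 the approximate MDES at ICC 0.05 is 0.41, above the stated 0.35.

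A reader might infer that power is overstated or that the trial is underpowered. The documents do not support either. Applying an assumed Bonferroni correction for two or eight tests to the 8/8 model lowers power at 0.35 (ICC 0.05) from about 80% to 70% or 46%. That, however, penalises a model that is not the design and leaves out what baseline may gain. The number of tests is also assumed, since calculating ratings for several food groups does not make them one family of co-primary tests.

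The 12-pair calculation has its own limit. It treats pairs as independent, although A2–D2 and A3–D3 each sit in two consecutive pairs, and the article plans multilevel models rather than a paired test for this outcome.

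**Conclusion.** Wrong as written. The stated 80% power for 0.17, 0.35 and 0.48 refers to an allocation that never occurs, to one time point instead of change, and to an alpha that the Analyses section says will be corrected. The concluding sentence credits a count that the calculation does not use.

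The direction of the discrepancy is open. At ICC 0.05 and uncorrected alpha, the approximate MDES runs from 0.41 down to 0.20 as r goes from 0 to 0.8, and it matches the stated 0.35 near r = 0.3. A correction that reaches the primary test would raise every value. These figures rest on the assumed r, on independent pairs and on no gain from matching. They show how far the stated figure could be off, not what the true power is.

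**What to change.** Replace the 8/8 calculation with an MDES for the intervention effect on baseline-to-post change under the planned multilevel model. It should use:

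- 12 Intervention and 12 Control school-periods;
- a school random effect that accounts for the 8 re-used schools;
- ICC from 0.01 to 0.10 and a stated range of baseline-to-post school correlation;
- the alpha of the primary test: either designate overall FV consumption as the single primary test at 0.05, or use the corrected alpha.

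Replace the sentence about 14,160 observations with one based on the number of schools and pairs.

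The cost is text and one recalculation. The stated figure may become less favourable.
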